### Aims

The present study aims to evaluate the feasibility and potential effectiveness of two lifestyle interventions, information technology-assisted self-management alone (the SM intervention) or SM combined with care management by a dietitian and exercise counselor (the CM intervention), in comparison to usual care (UC). The primary hypothesis for each intervention (SM and CM) is that intervention participants will achieve greater reductions in body mass index (BMI) than UC participants at 15 months. Secondary research goals include comparing the effects of each intervention to UC on changes in glycemic control (fasting blood glucose and hemoglobin A1c), additional cardiovascular risk factors (serum lipids, blood pressure, waist circumference, and C-reactive protein [CRP]), health-related quality of life and psychosocial well-being. Differences between CM and SM intervention effects on weight loss and secondary outcomes also will be examined. Potential mediators (e.g., treatment adherence, caloric intake, physical activity level) and moderators (e.g., age, gender, race/ethnicity, baseline mental status) of the intervention effects on weight change and secondary outcomes will be explored. Additionally, process measures will be evaluated to assess the extent of participation of patients in each intervention and the potential reach, adoption, implementation and maintenance of the interventions in primary care practice.

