**Inclusion criteria**
1. Ethnicity: All ethnic groups;
2. Gender: Men and Women;
3. Age (as of date of enrollment):
a). Lower age limit: 18 years;
b). Upper age limit: NONE (*only exclude for cause, e.g. diseases, functional limitations detailed below*);
4. Body mass index ≥ 25.0 kg/m^2^;
5.Having pre-diabetes and/or metabolic syndrome based on the following criteria:
a). Pre-diabetes: fasting plasma glucose between 100 and 125 mg/dL;
b). Metabolic syndrome: Three or more of the following:
--Waist circumference ≥ 40 inches in men; ≥ 35 inches in women (if in Asian American ≥ 35 inches in men; ≥ 31 inches in women);
--Triglycerides ≥ 150 mg/dL;
--High-density lipoprotein cholesterol (HDL-C) < 40 mg/dL in men; < 50 mg/dL in women;
--Systolic blood pressure ≥ 130 mm Hg or diastolic blood pressure ≥ 85 mm Hg;
--Fasting plasma glucose between 100 and 125 mg/dL.
6. Having a primary care physician (PCP);
7. Able and willing to enroll and provide written, informed consent, i.e., to: 1) meet the time and data collection requirements of the study; 2) be randomized to one of the three intervention arms; 3) adhere to the recommendations of the study intervention as assigned; 4) participate in follow-up for 12 months; and 5) allow extraction of relevant information from their medical records.

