### Recruitment and Screening Process

Target sample size for E-LITE is 240, recruited in three sequential cohorts. The screening process for each cohort begins with identification using relevant data available in the patient's electronic health record of age-appropriate, potentially eligible patients whose primary care provider (PCP) regards the interventions under study to be medically appropriate and safe for that patient. Patients whose participation is approved by their PCP are asked to complete a brief questionnaire regarding major exclusions, either online or by phone. Those who pass the initial screen are scheduled for a formal eligibility determination (baseline) visit (BV1), and, within two weeks prior to the visit, they are contacted and given instructions for completion of an online baseline questionnaire.

The BV1 occurs no more than four months after the initial screen and no more than four weeks prior to randomization. It includes completion of additional eligibility questionnaires, measurement of height, weight, waist circumference, and resting blood pressure, and a fasting blood draw for tests of plasma glucose and lipids at the onsite Clinical Laboratory. Time permitting, a seven-day physical activity recall [24] is completed; otherwise, it will be completed at the baseline assessment/randomization visit (BV2). Participants are given instructions and a three-day food record form to be completed and returned at BV2. Participants who have possible angina or peripheral vascular disease based on the Rose Questionnaire [25] are referred to their PCP for further evaluation and may only continue with explicit authorization of their physician.

Participants who are eligible to continue on the basis of BV1 are scheduled for BV2, which occurs at least seven days after BV1 and no more than three weeks prior to the start of the intervention. The BV2 includes measurement of weight, waist circumference, and resting blood pressure, a review of the three-day food record for completeness, complete review of medication and supplement use, a non-fasting blood draw for tests of A1c and CRP, and if necessary, completion of the physical activity recall. Following the measurements, participants are randomized.

All participants are properly and adequately informed and give appropriate consent at each step in the screening process of the trial and prior to participating in the post-randomization phase.

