### Data Analysis

The primary hypothesis compares BMI between each intervention (SM and CM) and usual care at 15 months using an intent-to-treat analysis. Linear mixed modeling,

using SAS PROC MIXED [54] will test time and group interactions to asses whether within-subject change in BMI differs by condition. This basic analytical strategy also accounts for the nature of repeated measurements, the blocked design by cohorts, and the clustering of patients within physicians. The same analysis strategy is appropriate for evaluating secondary aims where the hypotheses are identical but with different outcome measures (e.g., glycemic control, other component risk factors of the metabolic syndrome, and psychosocial well-being). The longitudinal effects of the interventions will be assessed using the same model, except that the focus is comparisons within intervention groups at different time points. Analyses will also be conducted to examine whether there is a dose-response relationship between intervention adherence and outcome, where dose is defined in terms of number of group sessions attended, number of secure messages sent, number of self-monitoring logs, average daily intakes of calories and fat, and average number of minutes of physical activity per week.

For participants with missing outcomes at the primary (15-month) or secondary (3- and 6-month) assessment point, we will conduct and report on sensitivity analyses in which different imputation methods are used (e.g., the baseline-observation-carried-forward method, the "hot deck" procedure, and an appropriate multiple imputation method [55,56].

We will use the MacArthur approach, which modified the Baron & Kenny criteria, for defining moderators and mediators in clinical research studies [57]. Let T be the treatment, M be the potential moderator or mediator, and O be the outcome. Association between T, M, and O is examined using the following models:(1)

M is a moderator of the effect of T on O if M precedes T, γ_1 _= 0, and β_3 _≠ 0. M is a mediator of the effect of T on O if T precedes M, γ_1 _≠ 0, and either β_2 _≠ 0 or β_3 _≠ 0.

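### The longitudinal effects of the interventions are to be read from within-arm changes, which cannot separate an effect from regression to the mean or drift; they should be contrasts with usual care

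*Protocol article*

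**What the plan says.** The Data Analysis section describes two layers of analysis.

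The first is between arms and fixed in time: "The primary hypothesis compares BMI between each intervention (SM and CM) and usual care at 15 months using an intent-to-treat analysis". The mixed model "will test time and group interactions to asses whether within-subject change in BMI differs by condition". The Aims section agrees, since its hypothesis is that "intervention participants will achieve greater reductions in body mass index (BMI) than UC participants at 15 months". The same strategy is extended to the secondary outcomes, including glycemic control and the metabolic-syndrome components.

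The second layer is separate: "The longitudinal effects of the interventions will be assessed using the same model, except that the focus is comparisons within intervention groups". These comparisons run from one visit to another, and no comparison with usual care is named for them.

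Two design features bear on this second layer:
- **Entry thresholds.** Participants enter on measured thresholds, for example "Pre-diabetes: fasting plasma glucose between 100 and 125 mg/dL", with further thresholds for triglycerides, HDL-C, waist and blood pressure (Table 1, inclusion item 5).
- **Baseline visits.** Under Recruitment and Screening Process, BV1 is the eligibility visit and includes "a fasting blood draw for tests of plasma glucose and lipids at the onsite Clinical Laboratory". BV2 repeats weight, waist and blood pressure. Its blood draw is non-fasting and covers only A1c and CRP. The only listed baseline values of fasting glucose and lipids are therefore the qualifying ones.

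**The concern.** The sentence does not leave the longitudinal analysis open. It assigns the effects of the interventions to before-after comparisons inside an arm. When people are selected because a noisy measurement crossed a threshold, their next measurement tends to lie closer to their usual level, with or without a program. Seasonal or secular change and the attention that comes with trial participation also move an arm over time. Randomization with a concurrent usual-care arm removes all of these, but only if the comparison is made between arms.

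At stake are the longitudinal claims: statements that a program lowered glucose or improved lipids over 6 or 15 months, supported by a within-arm p-value that an inert program could also have produced.

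**Working it through.** **1. The plan's own figure.** From the Sample Size section: N = 240, 1:1:1 allocation, up to 20% loss, effect 0.5 SD, two-sided 0.05, t-test. Per arm, 240/3 = 80 and 80 × 0.8 = 64 evaluable. The noncentrality is 0.5 × √(64/2) = 2.83 on 126 df, which gives 80.1% power (80.7% by the normal approximation). The stated figure of about 80% is reproduced. It belongs to the between-arm contrast at 15 months.

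**2. Drift common to all arms, no treatment effect.** Let every arm move by d SDs of change (d is assumed). A one-sample t-test within an arm of 64 has noncentrality d × √64 = 8d.

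| d | 8d | within-arm test significant | between-arm test |
|---|---|---|---|
| 0.1 | 0.8 | 12% | 5% |
| 0.2 | 1.6 | 35% | 5% |
| 0.3 | 2.4 | 66% | 5% |
| 0.5 | 4.0 | 98% | 5% |

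The between-arm test stays at 5% because the expected difference is d − d = 0.

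**3. Fasting glucose, with entry at 100-125 mg/dL.** These inputs are assumptions, not in the documents: population mean m of 90 to 100 mg/dL, SD 10, single-measurement reliability r of 0.6 to 0.8, no treatment effect.

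- Expected fall among the glucose-qualified = (1 − r) × (E[X | 100 ≤ X ≤ 125] − m).
- E[X | 100 ≤ X ≤ 125] = m + 10 × [φ(a) − φ(b)] / [Φ(b) − Φ(a)], with a = (100 − m)/10 and b = (125 − m)/10. This is 105.22 for m = 90 and 107.72 for m = 100.
- Variance of change = (1 − r)² × Var(X | 100 ≤ X ≤ 125) + 100 × (1 − r²).

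Largest case (m = 90, r = 0.6): the fall is 0.4 × 15.22 = 6.09, SD of change 8.19, noncentrality 8 × 6.09/8.19 = 5.95, significant in about 100% of trials.

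Smallest case (m = 100, r = 0.8): the fall is 0.2 × 7.72 = 1.54, SD of change 6.10, noncentrality 8 × 1.54/6.10 = 2.02, significant in 51%.

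**4. Not everyone qualifies on glucose.** Metabolic syndrome alone is enough for entry. Let a share q qualify on glucose and draw the rest from X < 100, where the mean is 87.12 (m = 90) or 92.02 (m = 100). That group regresses upward: by 0.4 × (90 − 87.12) = 1.15 in the first case and 0.2 × (100 − 92.02) = 1.60 in the second. Each cell gives the arm's mean fall in mg/dL, the SD of change and the share of trials significant.

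| q | m = 90, r = 0.6 | m = 100, r = 0.8 |
|---|---|---|
| 100% | 6.09, SD 8.19, 100% | 1.54, SD 6.10, 51% |
| 75% | 0.75 × 6.09 − 0.25 × 1.15 = 4.28, SD 8.87, 97% | 0.75 × 1.54 − 0.25 × 1.60 = 0.76, SD 6.26, 16% |
| 50% | 0.5 × 6.09 − 0.5 × 1.15 = 2.47, SD 9.15, 57% | 0.5 × 1.54 − 0.5 × 1.60 = −0.03, SD 6.31, 5% |

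If pre-screening on health-record data raises the mean before BV1 to 105 (assumed), the range with everyone glucose-qualified is 21-39%.

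**The case against.** **Between-arm tests already exist.** The secondary aim compares each intervention with usual care, and the Data Analysis section applies the between-arm strategy to glucose and the other risk factors. A reader of the results would see those tests as well. This stands, and it confines the harm to whatever is reported as a longitudinal effect. It does not make a within-arm change a valid estimate of such an effect.

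**The phrase may cover all three arms.** Table 1 refers to three intervention arms, so usual care's own change might be shown alongside. That would help a careful reader, but setting one arm's p-value beside another's does not test their difference. With a common drift of 0.3 SD, an intervention arm would be significant and usual care not in about 0.66 × 0.34 = 22% of trials, with no effect at all.

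**The glucose figures depend on who enrolls.** This also stands. The 51-100% range is the extreme in which every completer qualified on glucose, so the lower ranges are shown with it. Waist and blood pressure are re-measured at BV2. A1c and CRP are not entry criteria.

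**A stronger reading is tempting.** Because the model tests time and group interactions, a reader might infer that the primary test is a 6-df omnibus interaction, which an early effect lost by 15 months could make positive. The documents do not support this. No degrees of freedom or coding of time is stated. The abstract, Aims, Sample Size and Data Analysis sections all fix the comparison with usual care at 15 months. The Sample Size section names two key contrasts, each with its own p-value judged at 0.05, which one omnibus test could not supply. Data Analysis calls months 3 and 6 secondary: "For participants with missing outcomes at the primary (15-month) or secondary (3- and 6-month) assessment point". A 15-month group-by-time contrast is itself a time-by-group interaction and fits the wording. The exact contrast is detail for an analysis plan that is not shown.

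**Conclusion.** The point holds for the longitudinal sentence only. As written, it attributes to the interventions changes that may be regression to the mean, drift or trial participation. With no treatment effect, a within-arm glucose test could be significant in anywhere from 5% to nearly 100% of trials, depending mainly on the share of participants who qualified on glucose, while the between-arm test holds its 5%. The ranges rest on the assumed mean, SD and reliability and on normal distributions. Fasting glucose and lipids are most exposed; weight, waist and blood pressure less so.

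A reader might also infer that regression to the mean could make the primary BMI test positive. It could not: movement shared by randomized arms cancels in any group-by-time comparison. The primary and secondary comparisons with usual care stand as planned.

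**What to change.** Replace the sentence so that longitudinal effects are between-arm differences, SM-UC and CM-UC, estimated from the same mixed model with confidence intervals:

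- in change from baseline at each visit where the outcome is measured. By Table 2 this is months 3, 6 and 15 for weight, waist and blood pressure, months 6 and 15 for glucose, lipids and A1c, and month 15 for CRP;
- for maintenance, in change from month 3 or 6 to month 15, starting from month 6 for outcomes without a month-3 measurement.

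Within-arm changes can still be reported for all three arms as description, without being called intervention effects. The cost is wording and a different set of contrasts from a model already planned. No new data are needed. Sample size and power are unchanged: 64 evaluable per arm still gives 80.1%, because that calculation is already for the contrast with usual care.

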**Questionnaires**				
Demographics	X			
Family medical history	X			
Three-day food record	X	X	X	X
Eating Habits Confidence Survey	X	X	X	X
Social Support and Eating Habits Survey	X	X	X	X
Stanford Seven-day Physical Activity Recall	X	X	X	X
Exercise Confidence Survey	X	X	X	X
Social Support and Exercise Survey	X	X	X	X
Smoking and alcohol consumption	X			X
12-item Short Form Health Survey (SF-12)	X	X	X	X
Obesity Related Problems Scale	X	X	X	X
Nine-item Patient Health Questionnaire (PHQ-9)	X	X	X	X
Depression Anxiety Stress Scale	X	X	X	X
Symptoms	X	X	X	X
Adverse events		X	X	X
Medication use	X	X	X	X
Care at non-PAMF health care facilities	X	X	X	X
Unified Theory of Acceptance and Use of Technology^1^		X	X	X

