Recommendations are also given for total fat reduction (to 25% of calories from fat) and calorie balance and restriction (with a goal of a 500- to 1000-calorie reduction diet). As in the DPP [7], the calorie and fat goals are given as a means to achieve and maintain the weight goal, rather than as a goal in and of itself. Therefore, if a participant consumes more than the assigned calorie or fat goal, but is achieving the weight goal, there is no need to focus on further reductions. Portion control, choices of low-energy and nutrient-dense meals and snacks, healthy food preparation techniques, and careful selection of restaurants, including fast food, and the items offered are promoted as strategies to gradually achieve the calorie and fat goals. Participants also are recommended to (1) lower saturated fat intake to < 10% of caloric intake, (2) lower cholesterol intake to < 300 mg/day, (3) consume a high plant-based diet that includes a variety of fruits and vegetables, whole grains, and low-fat dairy products, and (4) reduce intake of high glycemic index carbohydrates.

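### The dietary dose is named as an intake level with no reference to baseline, although the calorie goal is a reduction and the fat goal a share of calories

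*Protocol article*

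**What the plan says.** Under Data Analysis, the protocol article plans to examine a "dose-response relationship between intervention adherence and outcome, where dose is defined in terms of number of group sessions attended". The list continues with secure messages sent, self-monitoring logs and, last, "average daily intakes of calories and fat, and average number of minutes of physical activity per week". For the dietary items it gives no baseline reference, no comparison with an assigned goal and no unit for fat.

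Under Evidence-based Intervention Goals, both intervention arms receive recommendations. The one on calories comes "with a goal of a 500- to 1000-calorie reduction diet", and the one on fat sets a target of 25% of calories. The same section treats these two targets as serving the weight goal and not as ends in their own right. It says that no further reduction is needed "if a participant consumes more than the assigned calorie or fat goal" while the weight goal is being achieved.

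The "Three-day food record" is scheduled in Table 2 at baseline and at months 3, 6 and 15. Data Management plans a nutrient analysis of these records. Potential Mediators names them as an adherence instrument.

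**The concern.** A dose meant to capture adherence should rise or fall with how closely a participant followed the prescription. The calorie prescription is relative to the person. Someone who starts high and makes a full cut can still eat more than someone who starts low and changes nothing. An intake level therefore carries habitual intake along with adherence. The activity item in the same list does not have this difficulty, because its goal of 150 minutes a week is itself a level.

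The stake is interpretive. A real relation between cutting calories and BMI could look weak or absent, and a null result could then be read as showing that dietary adherence does not matter.

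**Working it through.** **The design figure.** The article's power statement reproduces. With 240 / 3 = 80 per arm and 20% loss, 64 per arm remain. For a 0.5 SD difference at two-sided 0.05, the normal approximation is 0.5 × √(64/2) − 1.96 = 0.868, which gives 80.7% power (80.1% with the noncentral t) against the stated 80% or so. Nothing below touches this figure.

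**Example (intakes are illustrative, not from the article).**

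| | Baseline kcal | Follow-up kcal | Cut | Fat, g | Fat, % of calories |
|---|---|---|---|---|---|
| A | 3000 | 2300 | 700 | 64 | 9 × 64 / 2300 = 25.0 |
| B | 1700 | 1700 | 0 | 57 | 9 × 57 / 1700 = 30.2 |

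A makes a cut within the 500 to 1000 range and is at 25% fat. B makes no cut and is above 25%. Ranked by follow-up calories, or by fat if it is counted in grams, B appears the better adherer.

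**General size.** Let B be baseline intake, R the true reduction, and I = B − R the follow-up intake. Let r be the correlation of B with R. Then

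corr(−I, R) = (SD_R − r·SD_B) / √(SD_B² + SD_R² − 2r·SD_B·SD_R).

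The article gives none of these inputs. Assumed: SD_B 400, 600 or 800 kcal/day; SD_R 250, 350 or 500; r 0, 0.3 or 0.5; mean reduction 400. Middle case, SD_B = 600 and SD_R = 350:

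- r = 0: 350 / √482,500 = 350 / 694.6 = 0.50 (squared, 25%)
- r = 0.3: (350 − 180) / √356,500 = 170 / 597.1 = 0.28 (8%)
- r = 0.5: (350 − 300) / √272,500 = 50 / 522.0 = 0.10 (1%)

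Extremes over the 27 settings:

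- Lowest (SD_B 800, SD_R 250, r 0.5): −150 / 708.9 = −0.21
- Highest (SD_B 400, SD_R 500, r 0): 500 / 640.3 = 0.78

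The correlation is negative when SD_R < r·SD_B. That occurs in 3 of the 27 settings, all at r = 0.5.

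**Mis-ranked pairs.** Take pairs in which only one person reached a 500 kcal cut. In simulation, low intake ranks that person as the worse adherer in about 27%, 37% and 46% of pairs in the middle case (r = 0, 0.3, 0.5). Over the grid the range is 13% to 60%.

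**A second set of assumptions** (baseline SD 200 to 800, reduction mean 500 and SD 300, r 0 to 0.6) gives rank correlations from 0.82 down to −0.25, with 19% to 59% of pairs ranked the wrong way round.

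**With baseline in the model.** Since I = B − R, a linear model containing I and B is a re-expression of one containing R and B, and the coefficient of I is exactly minus that of R. The baseline-adjusted residual of I has correlation √(1 − r²) in absolute value with R: 1.00, 0.95 and 0.87 at r = 0, 0.3 and 0.5. In the second simulation the rank correlations are 0.78 to 1.00. These figures ignore reporting error in the food records.

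**The case against.** The strongest reply is that the article fixes no scoring rule. It lists kinds of measure, without scaling, model or covariates, and does not call the intakes absolute. A condensed article may leave such detail to a fuller document. Baseline food records exist, and adjusting for them removes most of the problem. This stands in part: adjustment is unstated, not excluded. But the article does name the dietary variable, and the variable it names does not match the calorie prescription, so the wording itself is worth correcting.

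The reply is stronger for fat. No unit is given, and the goals section expresses saturated fat as a share of calories, so fat as a percentage is a fair reading. The gram comparison in the example applies only if grams are meant.

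The benchmark is also partly open. The article does not say that the calorie cut is counted from the baseline food record, and it refers to an assigned goal. Whether a given participant counts as non-adherent depends on that goal, which is not shown. The diet goals are also secondary to the weight goal.

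That lower intake means better adherence, unlike the other dose items, is no defect. No composite is described, so the coefficient simply takes the opposite sign.

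**Conclusion.** The point holds as a mismatch of wording with a conditional consequence. If follow-up calories enter unadjusted, the dose mixes adherence with habitual intake, and its association with BMI can be attenuated. How far depends wholly on assumed inputs, and the range of correlations covers both a usable and a nearly useless measure.

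A reader might infer that the plan scores participants on absolute intake, that the analysis cannot answer its question, or that the association is likely to reverse. The article supports none of these. It sets no score and does not rule out baseline adjustment. Reversal appears only in a small corner of the assumed grid, where larger eaters cut considerably more.

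The scope is one supportive, non-randomised analysis. The session, message, log and activity measures are unaffected, as are the primary intent-to-treat comparison of BMI and its power. The change is worth making because it costs almost nothing; it is not essential to the trial.

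**What to change.** In Data Analysis, replace the dietary item with follow-up average daily calories adjusted for baseline intake and, for fat, percent of calories. Change in calories from the baseline three-day food record is an acceptable alternative to the adjusted form. The two are not identical, so the plan should name one.

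The cost is wording only, since the baseline and follow-up records and the nutrient analysis are already planned. A change score carries the reporting error of two records, which is a reason to prefer adjustment for baseline. No dietary goal or participant procedure changes.
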